# Abstract / Summary

Objective: The objective of this intervention is to improve engagement and retention in clinical care for HIV-infected individuals at high risk of disengagement from medical care on Mfangano, Remba and Ringiti Islands, Kenya.

Design: Individual parallel groups randomized controlled trial.

Subjects: *Selection Criteria:* Patients in HIV care at any of eight target clinics on Mfangano, Remba and Ringiti islands who miss a clinic appointment by >3 days. *Recruitment:* During the recruitment period, individuals meeting eligibility criteria will be enrolled in the study and will receive a brief counseling session identifying barriers to care and encouraging return to clinic. Index participants meeting above eligibility criteria will be randomized to either the microclinic or control arms. Those randomized to microclinic arm will be invited to recruit members of their social support network to form a ‘microclinic’ group of 5-10 individuals and will then proceed through the intervention. Control arm index participants will not form microclinic groups during the study, but will be invited to form microclinic groups after the completion of the study.

Intervention: *Intervention HIV Curriculum*: 7 bi-weekly group sessions on HIV-related topics incuding HIV biology, antiretroviral medications and group treatment support, in addition to a facilitated HIV status disclosure session.

Measurements: *Primary outcomes*: 90 day absence from clinical care; Engagement in HIV care over 12 months, as measured by proportion of time in clinical care. *Secondary outcomes*: Time to return to care; alive and retained in care at end of study; virologic suppression at 12 months.

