## Sampling

*Sample Size Calculation*

Sample size calculations were generated based on preliminary data from the Mfangano Island Healthy Network Impact Study (MIHNIS). The MIHNIS study was a quasi-experimental study with the intervention delivered to one community and neighboring communities acting as control groups. Additionally, the proposed clinic sites were visited in September 2014 to assess rates of missed clinic appointments to help ground sample size estimates in the realities of each individual clinic.

During the six months prior to delivery of the intervention in the MIHNIS study, 268 of 410 (65%) patients on ART at the Sena Health Center missed a clinic visit by >3 days. Of these, 238 (89%) joined the study. Among the control group in the MIHNIS study, 36 of 145 (25%) participants who missed a clinic visit by more than 3 days during the 6 months enrollment period had a 90-day clinic absence within the following 12 months. Among patients eligible for the intervention and who missed a clinic visit by >3 days during the enrollment period, 72 of 93 (77%) actually participated in the microclinic intervention. In the MIHNIS study participants in the intervention community had a more than 50% lower rate of 90-day disengagement than those in the control community, regardless of intervention uptake.

Thus, we assume an event rate of 0.25 in the control group and 0.125 in the intervention group. Setting alpha to 0.05 and beta to 0.2 and assuming an average of 2 participants per group with a coefficient of variation of 0.25, we will need 156 index participants per study arm. This sample size accounts for non-independence of outcomes introduced by the clustered nature of the intervention. Allowing for 10% participant attrition, we would need to sample 175 participants per study arm. The MIHNIS study ascertained outcomes for 98.6% of study participants, thus the allowance for 10% attrition in the proposed study is conservative.

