The accessible population for this study includes all patients in HIV care and treatment, regardless of ART status, at the Sena (excluding patients residing in the East sub-location), Yokia, Ugina, Nyakweri, Wakula, Soklo, Remba and Ringiti Health Centers. Excluding patients residing in the Mfangano East sublocation from the total in Table 1, results in approximately 1500 current adult patients in these clinics. Extrapolating data from the MIHNIS study would suggest that 65% of these patients would become eligible for the Kanyakla Study during study enrollment. However, based on more recent observations at the included study clinics, we expect that only about half of the expected number of patients will become eligible. If we assume that 32% will become eligible that 75% of those who are elibigle will be willing to participate in the study, we will have an accessible population of 365 or approximately 180 per arm. Thus, because the accessible population is larger than the estimated sample size, we will extend our sample size to include up to 180 participants in each arm to allow for errors in these sample size calculations.

*Sampling Procedure*

Sampling will take place at included study clinics on a bi-weekly basis. Study staff will use information from the clinic daily activity log, master facility log and defaulter logs to identify all eligible patients who have missedclinic visits by >3 days. All eligible patients will be sampled for the study.

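### Two outcomes are declared primary but the trial is sized on one, and no rule says how the two results combine into a primary claim

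*Protocol*

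**What the plan says.** The Abstract / Summary (Measurements) gives the primary outcomes as "90 day absence from clinical care; Engagement in HIV care over 12 months, as measured by proportion of time in clinical care" and places three further outcomes below them as secondary. The Research Questions section has a separate directional hypothesis for each of the two.

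Data Analysis gives each its own test: a Cox model for 90-day absence (Hypothesis 1) and linear regression for time in care (Hypothesis 2). Neither has a stated significance level. The remark under Hypothesis 1 that the primary analysis is unadjusted sits beside the cluster adjustment of standard errors and does not concern multiplicity.

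The sample size (Sampling, Sample Size Calculation) uses 90-day absence only: "we assume an event rate of 0.25 in the control group and 0.125 in the intervention group". It is set up by "Setting alpha to 0.05 and beta to 0.2", "assuming an average of 2 participants per group with a coefficient of variation of 0.25", and concludes that "we will need 156 index participants per study arm". After attrition the target is 175 per arm, and the section then allows up to 180. Time in care has no effect size, standard deviation, alpha or power anywhere. The protocol does not rank the two outcomes, split alpha, set a testing order or require both.

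**The concern.** Two primary outcomes are acceptable if the plan says what counts as success. This protocol names two, tests each, and plans for one. The stated operating characteristics (5% error, 80% power) then describe the primary claim only if that claim means 90-day absence alone, and the protocol does not say so.

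This matters because Project Sustainability, the section on benefits to society, and Expected Application of the Results tie continuation, expansion and further funding to the intervention proving efficacious or successful, and success is never defined. If one primary outcome is significant and the other is not, the reading could be chosen after the results are known.

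**Working it through.** **1. Reproduce the plan's own figure.** Inputs from the Sampling section: p0 = 0.25, p1 = 0.125, alpha 0.05, power 0.80, m = 2 participants per group, coefficient of variation k = 0.25. The cluster formula for proportions, two-sided, is

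c = 1 + (1.96 + 0.842)² × [p0(1−p0)/m + p1(1−p1)/m + k²(p0² + p1²)] / (p0 − p1)²

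- Bracket: 0.09375 + 0.05469 + 0.00488 = 0.15332.
- Divided by 0.125² = 0.015625: 9.8125.
- Times 7.849: 77.02, so c = 78.02 groups, or 156.0 participants per arm.

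This matches the stated 156. A one-sided 5% test in the same formula gives 1 + (1.645 + 0.842)² × 9.8125 = 61.7 groups, about 123 per arm. Two-sided testing is therefore a sound inference, though it is not stated. For attrition, 156/0.9 = 173.3, or 174 against the stated 175, which is immaterial. The sample size is correct for 90-day absence and uses the full 0.05 for it.

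**2. Error rate if either outcome suffices.** Assume two two-sided 0.05 tests whose statistics are bivariate normal with correlation r. The protocol gives no r, so a range is shown.

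- Either direction: 1 − P(|Z1| < 1.96, |Z2| < 1.96). At r = 0 this is 1 − 0.95² = 0.0975.
- In favour of the intervention only: 1 − P(Z1 < 1.96, Z2 < 1.96). A single test gives 2.5%.

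| Assumed r | Either direction | In favour of intervention |
|---|---|---|
| 0 | 9.75% | 4.9% |
| 0.5 | 9.1% | 4.5% |
| 0.8 | 7.8% | 3.9% |
| 0.9 | 7.0% | 3.5% |
| 0.95 | 6.5% | 3.2% |
| 0.99 | 5.7% | 2.8% |

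**3. Where r might lie.** Under Hypothesis 2, days out of care are the summed gaps between missed appointments and the next visits. A 90-day absence therefore adds directly to them, and a clear positive association is expected. As an illustration, null trials with 180 per arm, 25% events and no clustering were simulated (20,000 each), with a two-proportion test and a comparison of means. Days out of care were given three invented distributions:

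- Absence 90–150 days, others 0–150: patient-level correlation about 0.45 in size, error 9.5%.
- Absence 90–290 days, others 0–120: about 0.80, error 7.8%.
- Absence 90–290 days, others 0–30: about 0.93, error 6.6%.

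These agree with the table. They show its plausible span but do not estimate r for this trial.

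**4. If both outcomes must be significant.** The chance of a false joint claim is at most 5%. Joint power, however, cannot exceed the power of either test. With 156 analysed per arm it is at most the planned 80%. If time in care also had 80% power (an assumption, as none is stated), joint power would lie between 0.80 × 0.80 = 64% for independent tests and 80% for completely overlapping ones. Enrolling 180 and losing 10% leaves 162, where the step 1 formula gives about 81% power for 90-day absence, so the ceiling barely moves.

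**The case against.** The strongest reply is that the protocol never says a win on either outcome makes the trial positive. It poses five questions and gives each an analysis. The alpha in the Sampling section is a planning input, not an allocation of error between outcomes. A statistical analysis plan, which was not available here, might state the rule, and multiplicity is commonly settled there.

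Much of this stands. A reader might infer that the trial's false-positive rate is 7% to 10% instead of 5%. The documents do not support that as a property of the trial, for three reasons:

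- It requires the either-suffices rule and two-sided tests, neither of which is written.
- It counts false findings of harm as well as benefit. In favour of the intervention, the chance stays below 5% even at r = 0.
- The outcomes overlap by construction, so independence is an unlikely extreme and the figure could fall to about 6%.

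The mismatch itself remains. How many outcomes are primary, and which one the sample size serves, are choices this protocol has already made, and they do not agree. Reading the plan as requiring both outcomes does not remove the problem; it moves it from the error rate to the power.

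**Conclusion.** The point holds as a mismatch between two declared primary outcomes and one powered test, with no stated rule joining them. The size of the consequence depends on which rule is meant:

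- Either suffices, each at two-sided 0.05: family-wise error about 6% to 10% for assumed correlations from about 0.95 down to 0. In favour of the intervention it is 3.2% at 0.95, 3.5% at 0.9 and 4.9% at 0, against 2.5%.
- Both required: no inflation, but 80% is only an upper bound on the power of the primary claim at the calculated size.

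The sample size for 90-day absence reproduces and is not in question. The change is worth making before any comparison by arm, since the current text leaves the definition of success open.

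**What to change.** In the Abstract, name 90-day absence as the single primary outcome at two-sided 0.05, and list time in care as the next outcome in a fixed sequence. In Data Analysis, add that Hypothesis 2 is tested confirmatorily at two-sided 0.05 only if Hypothesis 1 is significant, and that its estimate and confidence interval are reported in every case.

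This holds the error across the two outcomes at 5%, keeps full alpha for 90-day absence, and leaves the sample size and its power unchanged. It costs a sentence or so in each section. The real downside is that, if 90-day absence is not significant, time in care cannot support a confirmatory claim however strong its result.

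Other rules would also be valid if the investigators want both outcomes to stay primary, at a price. Testing each at 0.025 lowers power for 90-day absence, by the same cluster formula, from 80% to 71% at 156 per arm and from 85% to 78% at 180. Restoring 80% needs about 190 per arm, or 212 with 10% attrition. Requiring both outcomes needs a power calculation for time in care and for the joint claim.

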# Introduction/Background

The global health community has made tremendous progress in the scale-up of antiretroviral therapy (ART) over the past decade, with 9.7 million people accessing ART worldwide by the end of 2012. Importantly, there is now substantial evidence supporting anti-retroviral treatment as prevention, demonstrating that reductions in community viral load and infectivity can contribute to a decrease in new HIV infections.[3](#_ENREF_3)

Despite this progress, retention in lifelong HIV care and treatment remains a major challenge. One estimate indicates that fewer than one third of patients diagnosed with HIV in sub-Saharan Africa are consistently retained in care until ART eligibility.[4](#_ENREF_4) Countless others continue to be lost to follow-up at various stages along the continuum of HIV care.[5-7](#_ENREF_5) This sub-optimal provision and maintenance of treatment severely curtails the potential impact of ART within high-prevalence populations.[1](#_ENREF_1) If ART is to be scaled and optimally implemented, comprehensive strategies to address these gaps along the continuum of HIV care need to be developed. We argue that such strategies must recognize the central role that social environment plays in an individual’s ability to engage with HIV testing and clinical care.

Given the magnitude of the retention challenge, there is considerable interest in understanding barriers and facilitators of engagement in care over time. Numerous studies have identified HIV-related stigma as a key barrier to engagement in long-term HIV care in sub-Saharan Africa.[8](#_ENREF_8) In a large ethnographic study across three sub-Saharan African countries, Ware et al found that access to social capital was among the most important facilitators of good adherence to therapy.[9](#_ENREF_9) Investigators in that study found that patient support networks provided critical psychosocial and material resources for maintaining engagement in HIV care and adherence to therapy and, in return, expected ‘good adherence’ from the patients they were supporting. This exchange of support for positive health-seeking behavior is an important function of social networks for maintaining good health.

However, our own ethnographic field work suggests that such social capital is often difficult to access when seeking support for HIV treatment.[10](#_ENREF_10) In large part, this is because HIV status disclosure to members of their social networks can be a difficult process for many newly diagnosed individuals to initiate.[11](#_ENREF_11) Consequently, HIV-infected individuals continue to endure intense stigma in isolation across rural Africa, often forced to seek care in secret, consume antiretroviral regimens covertly, and navigate challenging healthcare and economic decisions on their own.

Social interventions to promote the exchange of social capital for positive health behaviors have been previously developed. Some ART programs encourage patients to identify a ‘treatment supporter’ – a trusted individual who can provide assistance with clinic appointments and medications, as well as psychosocial support throughout the treatment process.[14-19](#_ENREF_14) Patient support groups allow patient peer-groups to exchange knowledge and experiences with the management of HIV and HIV care. These interventions are both made more powerful through facilitation of HIV status disclosure to close supporters or peers.[22](#_ENREF_22) However, by focusing on either a single treatment supporter or a group of patient peers, these interventions may not fully utilize the pre-existing social infrastructure within which patients exist on a day-to-day basis. This infrastructure is the source of social capital identified as so crucial by Ware and colleagues and may provide critical support for maintaining HIV treatment over lifetimes. We developed an intervention targeted at patient-defined social networks, intended improve support for HIV treatment among informal social groups. We seek to evaluate this intervention’s impact on engagement in HIV care among patients on ART at a rural health facility on Mfangano Island in rural western Kenya.

These at-risk social networks represent an important yet underutilized resource in sub-Saharan Africa for optimizing HIV & AIDS treatment across the entire “continuum of care,” from diagnosis to enrollment in care, initiation of ART and long-term health maintenance. To date, strategies that specifically engage social networks in HIV care remain scarce, cumbersome to implement at scale and poorly evaluated. On Mfangano Island, a remote island in the Kenyan waters of Lake Victoria, our team has developed a social network-based intervention known as the ‘microclinic’ model. Home to nearly 20,000 residents, Mfangano has limited electricity, no paved roads and a very limited health infrastructure. Clinical facilities are limited to a single Level 3 health center and several dispensaries located throughout the island.

A microclinic is not a small medical facility, but rather a therapy management collective comprised of a small group of 5-15 neighbors, relatives, and friends. Members of microclinics are trained together as a team over three to six months to provide psychosocial, nutritional, and treatment adherence support for network members who are struggling with HIV & AIDS. Microclinic group composition is intentionally not restricted by HIV-status and the microclinic’s explicit purpose is to learn how to better improve HIV care for all members of the broader community rather than focus on a particular individual. This network-oriented approach is a novel departure from disease-oriented models, such as patient support groups, composed of group members who are exclusively HIV-infected. Our model recognizes that engagement of natural social supports within existing networks is essential for maintaining lifelong HIV treatment.

A community health worker and health educator guide Microclinics through a series of discussion sessions over a period of several months. Topics range from the biology of HIV and ART, to stigma reduction, effective communication and community outreach strategies. Following completion of these sessions microclinic groups are invited to participate in a facilitated group counseling and testing session that allows participants to voluntarily disclose their HIV status to one another – a powerful way to solidify specific group support and establish an enduring social infrastructure for both treatment and prevention of HIV.

In 2012, we completed a successful proof-of-concept pilot consisting of 47 groups composed of nearly 550 community members on Mfangano Island in Kenya’s Lake Victoria. Participation included 70% of all patients on ART within pilot villages, and over 84% of all participants disclosed their HIV status to their group at the conclusion of the program. Early results indicate that the intervention resulted in a 50% reduction in patients disengaging from care (an absolute reduction from 20% in the control group down to 10% in the intervention group. We now seek to expand the intervention across all of Mfangano Island, and to neighboring Remba and Ringiti Islands, to include 300-400 patients at eight ART clinics. Half of these patients will be randomized to form microclinic groups with their social networks and the other half will be randomized to standard clinical care. Patients randomized to control conditions will be invited to recruit members of their social network to form microclinic groups and participate in the curriculum following completion of study follow-up.

# Justification

Group social support and social network interventions have great potential to improve engagement in lifelong HIV care in a cost-effective manner, however limited evidence is available to support roll-out of interventions of this type. Social support interventions often suffer from major selection bias in most research studies, leaving program implementers and policy makers with limited evidence to support decisionmaking around implementation of these programs. Social network interventions suffer from a different challenge. Though a literature is developing around interventions to promote HIV prevention among social networks, there is little to no evidence supporting social network interventions to promote engagement and retention in HIV *treatment*. By conducting a rigorous randomized trial of a social network intervention to optimize HIV treatment, we seek to address both of these challenges simultaneously. Our non-randomized pilot study conducted from 2011-2013 demostrated feasibility and suggested that the intervention substantially improves engagement in HIV care (publication in preparation). However, further evidence from a randomized trial is needed to support implementation on a wider scale. This study will provide the necessary evidence supporting both the efficacy of this intervention and the ability to implement it in ‘real world settings’. Implementation within FACES-supported Ministry of Health clinics will also enable more effective dissemination throughout other clinics in the Ministry of Health clinic network, should the intervention prove efficacious and effective.

# Research Questions

- 1. **Research Questions**

Among HIV-infected patients enrolled in HIV care at eight clinics on Mfangano, Remba or Ringiti Islands, Kenya who have missed a HIV clinic appointment by at more than 3 days:

- - 1. Does the Microclinic social network-based HIV intervention reduce gaps in clinical HIV care over 12 months of follow-up, as compared to standard of care?
    2. Does the Microclinic social network-based HIV intervention improve the proportion of time patients spend adhering to recommended clinic appointments over 12 months of follow-up, as compared to standard of care?
    3. Does the Microclinic social network-based HIV intervention reduce time to re-engagement in clinical HIV care, as compared to standard of care?
    4. Does the Microclinic social network-based HIV intervention improve retention in HIV care at 12 months of follow-up, as compared to standard of care?
    5. Does the Microclinic social network-based HIV intervention increase the proportion of patients who are virologically suppressed at 12 months of follow-up, as compared to standard of care?
  1. **Hypotheses**
     1. Participants randomized to the microclinic HIV intervention will have a lower incidence rate of 90-day absence from clinical HIV care over 12 months post-randomization than participants randomized to standard of care.
     2. Participants randomized to the microclinic HIV intervention will spend a larger proprotion of time ‘in care’ than those randomized to standard of care. Time in care is defined as the number of days a patient spends adherent to his or her clinic visit schedule divided by the total number of days the patient is observed. See measurement section below for more detail).
     3. Participants randomized to the microclinic HIV intervention will have a higher hazard of re-engagement in clinical care than those randomized to standard of care. Re-engagement is defined as attending an HIV clinic visit and receiving the patient’s ART prescription from the clinic pharmacy.
     4. A larger proportion of participants randomized to the microclinic HIV intervention will be retained in HIV care at 12 months than those randomized to standard of care. Retention is defined as being alive and not missing a clinic appointment by 90 days or more as of study closure at 12 months post-enrollment of the last study participant.
     5. A larger proprotion of participants randomized to the microclinic HIV intervention will be virologically suppressed at 12 months of follow-up than those randomized to standard of care.

